#### Acceptability of the intervention

Acceptability of the intervention among patients, relatives and physiotherapists will be measured by number of withdrawals (requested by patient, relative or healthcare professional), all of the points about under the heading “Process” in addition to qualitative data collected via semi-structured interviews with patient participants, their relatives and physiotherapists and a focus group with physiotherapists.

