The functional standing frame intervention combines two physiotherapy interventions that have separately been evaluated and reported in the literature: prolonged standing and task-specific strength training. Currently, it is not known whether this novel combination of physiotherapy for people with severe stroke is effective in everyday clinical practice, and the United Kingdom Medical Research Council provides guidance on how complex interventions can be developed and evaluated [42]. A key component of the evaluation of the complex intervention is the acceptability among people with severe stroke. Currently, it is not known whether the functional standing frame programme would be tolerated or acceptable for people with severe stroke, at this early stage of their rehabilitation continuum. The Medical Research Council guidance explicitly recommends an early phase of assessing feasibility prior to a full definitive main trial [43] and recognises the value of using both quantitative and qualitative methods concurrently. The use of qualitative research within feasibility RCTs is becoming increasingly common [48]. This feasibility randomised controlled trial facilitates the evaluation of acceptability, compliance and delivery of the intervention; trial practices, processes and design; and recruitment and refusal and retention rates. This links to the trial objectives and will inform the conduct and design of the anticipated definitive main trial to facilitate successful, effective and confident delivery.

Qualitative research will be embedded in this feasibility trial and used in tandem with quantitative methods to provide insights into the intervention and trial processes.

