**Table Taba:** 

Feasibility indicator	Outcome measures	Data collection method
Process		
Recruitment rate	% of participants recruited/time	Case Report Forms
Retention rate	% of participants completed T1, T2, T3, T4, T5	Case Report Forms & Withdrawal Forms
Ability to consent	% of participants consenting	Screening/Approach Logs
Consent rate	% of consultee declarations	Case Report Forms
Eligibility criteria	% of admissions screened & eligible	Screening/Approach Log, Recruitment rate, Interview & Focus Group
Willingness of physiotherapists to recruit	% of admissions screened & approached	Recruitment rate, Interview & Focus Group
Willingness of patients to be randomised	% of participants who refuse to enrol in the trial	Recruitment Rate, Interviews & Focus Group
Acceptability of the intervention	% of withdrawals	Case Report Forms & Interview
Determining usual physiotherapy	Frequency specific physiotherapy interventions are implemented	Case Report Forms
Resources		
Burden	% of participants refusing physiotherapy sessions and follow-up assessments	Case Report Forms & Interviews & focus group
Cost effectiveness	*n* = duration (minutes) of functional standing frame programme session	Case Report Forms & Interviews
Management		
Fidelity	Observe intervention and control group sessions	Fidelity Checklists
Participant adherence	*n* = sessions per week	Case Report Forms
	*n* = minutes in standing	Case Report Forms & interview
	*n* = sit to stand repetitions	Case Report Forms & interview
	*n* = Yes; *n* = No for enjoyment	Case Report Forms & interview
	Score out of 10 for effort	Case Report Forms & interview
	Score out of 10 for fatigue	Case Report Forms & interview
Orthostatic hypotension protocol	% incidence of orthostatic hypotension	Case Report Forms
	% of incomplete sessions due to orthostatic hypotension (OH)	Case Report Forms
Safety		
Intervention	*n* = AE & SAE	Adverse Event and Serious
Data collection	*n* = AE & SAE	Adverse Event Forms

T1: baseline; T2: post-intervention period; T3: 3 months; T4: 6 months; T5: 12 monthsB)Clinical outcome measures

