### Retention rates and withdrawal

Each participant has the right to withdraw voluntarily from the trial at any time, without any effect on their current or future care. This may be through personal choice (i.e. they withdraw their consent), where it becomes impossible to provide outcome data or comply with any other trial procedures for whatever reason, following consultation/recommendation of a health professional following an adverse event or serious adverse event, or a significant protocol deviation, such as a participant being found to be ineligible post-randomisation. Participants found to be ineligible will be withdrawn. Reasons for withdrawals will be recorded and reported by the treating physiotherapist using a standardised proforma. Participants who wish to stop participating in the functional standing frame group will be asked to remain in the trial for follow-up assessments as per protocol if this is possible, although it is acknowledged that if a participant is receiving end of life care this would not be appropriate.

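### The only dedicated acceptability count is trial withdrawals, which misses people who stop the frame programme but stay for follow-up and can include departures unrelated to it

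*Protocol article*

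**What the plan says.** Under Objectives, Process, Acceptability of the intervention, the protocol article says acceptability will be "measured by number of withdrawals (requested by patient, relative or healthcare professional". The same sentence adds the other Process indicators, "in addition to qualitative data collected via semi-structured interviews with patient participants, their relatives and physiotherapists and a focus group with physiotherapists". In the feasibility outcomes table, the acceptability row has one outcome measure, a percentage "of withdrawals", with case report forms and interview as sources. The row names no arm, period or reason.

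The section Retention rates and withdrawal shows how the article uses the word: "Each participant has the right to withdraw voluntarily from the trial at any time". Besides personal choice, the grounds include cases "where it becomes impossible to provide outcome data or comply with any other trial procedures for whatever reason", advice from a health professional after an adverse event, and ineligibility discovered after randomisation: "Participants found to be ineligible will be withdrawn". The section describes stopping the programme separately: "Participants who wish to stop participating in the functional standing frame group will be asked to remain in the trial for follow-up assessments".

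The programme lasts 3 weeks and follow-up runs to 12 months. Sessions completed and reasons for non-completion are recorded under Participant adherence, and refused sessions under Burden. Neither section is referred to from the acceptability objective.

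**The concern.** Acceptability is one of the main questions the trial exists to answer. The Background states: "Currently, it is not known whether the functional standing frame programme would be tolerated or acceptable for people with severe stroke". The most direct sign that a participant does not accept a 3-week programme is that they stop it. The chosen count instead registers whether a participant leaves the study, over a period that continues long after the programme has ended.

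The error can run in either direction. The more successfully the team persuades stoppers to remain for follow-up, which is good practice, the more favourable the acceptability figure becomes. Conversely, requested withdrawals by control participants, or by programme participants tired of later assessments, make the programme look less acceptable than it was. Those planning the definitive trial could be misled by either.

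**Working it through.** No stated figure of the plan is in dispute, so the check has two parts: how the text classifies participants, and an illustration of size.

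**Classification as written**

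- *Stops the frame programme, agrees to follow-up:* not a withdrawal from the trial, so not in the count. Retention divides those completing data collection at each later time point by those completing baseline, so this person also counts as a success there.
- *Stops the frame programme and leaves the trial:* counted.
- *Completes the 3 weeks, asks to leave at, say, 6 months:* counted, although the programme was finished.
- *Control participant asks to leave:* counted, unless the measure is restricted to one arm, which neither the text nor the table does.
- *Found ineligible, or unable to provide data:* outside the Objectives wording where nobody requested the withdrawal, but not excluded by the table row, which drops that limit.

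**Illustration**

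Inputs: 25 in the programme arm (target of 50 in the Sample size section, assuming equal arms). Assumed, because the documents give no such rates: s = 5 stoppers, a share r of them staying in the trial, and u unrelated withdrawals per arm, taken as different people.

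- True stopping rate = s/25 = 5/25 = 20%.
- Count in the programme arm = [s(1 − r) + u]/25.
- Count over both arms = [s(1 − r) + 2u]/50.

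| Stoppers who stay | u per arm | Programme arm | Both arms |
|---|---|---|---|
| 5 of 5 | 0 | 0/25 = 0% | 0/50 = 0% |
| 4 of 5 | 0 | 1/25 = 4% | 1/50 = 2% |
| 0 of 5 | 0 | 5/25 = 20% | 5/50 = 10% |
| 5 of 5 | 4 | 4/25 = 16% | 8/50 = 16% |
| 4 of 5 | 4 | 5/25 = 20% | 9/50 = 18% |
| 0 of 5 | 4 | 9/25 = 36% | 13/50 = 26% |

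The true rate is 20% in every row. In the fifth row the count agrees with it only because the two errors happen to cancel. A count of programme discontinuations within 3 weeks in the allocated arm gives 5/25 = 20% throughout.

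For scale, the approximate 95% half-width for 20% of 25 is 1.96 × √(0.2 × 0.8/25) = 15.7 percentage points. The largest departures in the programme-arm column, −20 and +16 points, are slightly larger than that sampling error.

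**The case against.** The strongest reply is that withdrawals are only one component. The acceptability sentence goes on to interviews and a focus group, which suit the question well, and the planned sample of about six programme-arm participants could include people who stopped and stayed. This stands: a reader might infer that acceptability rests on withdrawals alone, and the document does not say so. But interviews cannot give a rate, and the sampling plan has a stratum for people who decline or withdraw and none for those who stop and stay.

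Second, stopping is already recorded. Adherence tracks sessions and reasons for non-completion, and burden counts refusals. The provisional progression criteria ask for 80% of the programme arm to adhere to at least five sessions a week. With 5 of 25 stopping early, adherence can be at most 20/25 = 80%, so stoppers do bear on that criterion. It would be wrong to infer that the trial fails to collect these data or that a 0% withdrawal figure would conceal stopping altogether. What remains is that none of this is named as a measure of acceptability.

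Third, the acceptability text does not say withdrawals from the trial, and might mean withdrawal from the intervention. That reading is possible. However, the one section that explains withdrawal uses it for leaving the trial and uses different words for stopping the programme.

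Fourth, the Objectives wording counts only requested withdrawals, and reasons are recorded on a proforma. A reader might take the whole 30% loss implied by the expected 70% follow-up at 12 months as entering the indicator. It would not, since that loss is from all causes. Nor are all the other Process indicators settled before the intervention starts: retention is measured from the post-intervention visit to 12 months.

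Finally, an unseen full protocol or analysis plan may add an arm or a time window. That could reduce the over-count, but would not bring back stoppers who remain, because the stated event is withdrawal.

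**Conclusion.** The point holds as a moderate weakness of definition, not a gap in data collection. The only dedicated quantitative indicator of acceptability measures leaving the trial, at any time and in either arm. It omits those who reject the programme but stay, and it can include requested withdrawals that say nothing about the programme. Retention does not correct this, because it treats the same stoppers as successes. The qualitative work and the adherence and burden data offset it in part.

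The size cannot be derived from the documents. A reading of 0% to 36% in the programme arm for a true 20% depends on the assumed 5 stoppers and 0 to 4 unrelated withdrawals. If nobody stops the programme and stays, and nobody withdraws for unrelated reasons, the count is correct. The conclusion also assumes that withdrawal in the acceptability text carries the meaning given to it in Retention rates and withdrawal.

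**What to change.** In the acceptability objective and in the matching table row, define quantitative acceptability as the number and percentage of participants allocated to the frame programme who permanently stop it before the end of the 3 weeks. Give these by who asked for the stop (participant, relative or health professional) and by reason, and count them whether or not they remain for follow-up. The definition should say that moving on to work outside the frame because of improvement, which the Intervention section allows, is not a stop.

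Report withdrawal from the trial separately, by arm and as during or after the 3-week period, alongside retention. The qualitative data and the other Process indicators can remain as supporting information, with a cross-reference to the adherence and burden sections.

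The cost is a wording change in two places and one extra line in the results tables. Session records, reasons for non-completion and withdrawal reasons are already collected. If the forms, which are not shown, do not record who asked for a stop, one item is needed. No treatment or follow-up procedure changes.

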#### Determining usual physiotherapy

Determining usual physiotherapy management for people who have had a severe stroke receiving inpatient early sub-acute stroke rehabilitation will be captured by the Control Group Case Report Forms.

#### Sample size estimates

Sample size estimates, together with existing literature and standard deviation of the outcome measures, will help to inform power calculations for subsequent trials.

### Resource

#### Burden

Patient participant and physiotherapist burden will be measured by number of patient participants refusing therapy sessions and follow-up assessments. This will also be explored in semi-structured interviews with patients, their relatives and physiotherapists, focus group with physiotherapists, and field notes from blinded assessor.

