#### Cost effectiveness

Estimates of resource use and related costs for the delivery of Standing Practice In Rehabilitation Early after Stroke (SPIRES) will be measured through semi-structured interviews exploring time required for preparation for functional standing programme session. Duration of functional standing frame programme group session (total minutes) will be captured in the Case Report Form and will be compared with the duration (total minutes) of the usual physiotherapy (control) group.

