#### Participant adherence

The tolerance/adherence of the functional standing frame programme to people who have had a severe stroke will be measured by tracking (i) total number of sessions completed; (ii) total number of minutes standing; (iii) total number of sit to stand repetitions; (iv) enjoyment; (v) effort; (vi) fatigue; and (vii) reasons for non-completion of sessions, as documented by treating physiotherapists in the Case Report Form.

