### Standardisation of the intervention

Treating physiotherapists from each of the three healthcare sites will perform the interventions as part of their clinical role; the CI and a blinded assessor (employed specifically for one site) will undertake the assessments.

Use of standing frames is incorporated within undergraduate physiotherapy training and is a recognised core skill for neurological physiotherapists. To standardise and optimise implementation of the intervention, treating physiotherapists will receive face-to-face training and an information pack. This includes a written template of what is required to be undertaken within each session (Figs. 2 and 3) and a link to the trial website.

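### The only quantitative indicator named for physiotherapist burden is patient refusal, which does not measure staff load; sessions lost for staff or equipment reasons would show as lower adherence, not as burden

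*Protocol article*

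**What the plan says.** The Burden paragraph, under the Resource objectives of the protocol article, gives two groups one indicator: "Patient participant and physiotherapist burden will be measured by number of patient participants refusing therapy sessions and follow-up assessments". It then adds qualitative sources: "This will also be explored in semi-structured interviews with patients, their relatives and physiotherapists, focus group with physiotherapists, and field notes from blinded assessor".

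The Burden row of the feasibility outcomes table gives the percentage "of participants refusing physiotherapy sessions and follow-up assessments", with data from "Case Report Forms & Interviews & focus group". It lists no quantity measured on staff.

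Three other sections bear on staff load:

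- Cost effectiveness takes staff preparation time from "semi-structured interviews exploring time required for preparation for functional standing programme session". Session duration comes from the Case Report Form and "will be compared with the duration (total minutes) of the usual physiotherapy (control) group".
- Participant adherence tracks sessions completed in the frame programme and "reasons for non-completion of sessions, as documented by treating physiotherapists in the Case Report Form".
- Qualitative evaluation plans interviews with eight treating physiotherapists and a focus group open to all physiotherapists who deliver the trial.

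**The concern.** An indicator should move with the thing it is named for. A count of patients who decline sessions or visits reflects patient tolerance and willingness. It need not rise when the programme becomes harder for a ward team to deliver, and it may fall short of, or run against, the true staff load.

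This matters because the trial asks whether ward physiotherapists can deliver daily assisted standing as part of their clinical role, to patients who at entry cannot stand without support and two people. If sessions are missed because a therapist, an assistant or the frame is not free, the planned numbers record fewer completed sessions, under a heading about participants' tolerance and adherence. A shortfall in staffing could then be read as patients failing to adhere. The two problems call for different changes before a main trial, and the progression section allows a shortfall to be overcome if a solution can be found. Choosing a solution requires knowing the cause.

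**Working it through.** The protocol gives no figure or threshold for burden, so there is none to reproduce. The check compares what the indicator counts with what loads staff, and then gives a scale.

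**1. Refused follow-up assessments.** Standardisation of the intervention says that "the CI and a blinded assessor (employed specifically for one site) will undertake the assessments". The treating physiotherapists deliver the sessions. A refused assessment therefore carries no information on their load.

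**2. Refused therapy sessions.** If a patient declines, the session is not delivered, and staff work on that day may fall. The count can move in the opposite direction to the load.

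**3. Sessions lost or cut short for lack of staff or equipment.** No patient has refused, so these add nothing to the count. The Intervention section leaves staffing per stand variable (one or more physiotherapists, with an assistant if needed), so such losses are plausible. Their frequency is not given.

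**4. Zero refusals.** From steps 1 to 3, a refusal count of zero is compatible with any level of staff load.

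**5. Do the other planned numbers fill the gap?**

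- *Session minutes by arm.* The frame arm is planned at up to 30 minutes in the frame plus 15 minutes of usual physiotherapy, 30 + 15 = 45. The control arm is planned at 45 minutes. The two arms have the same target by design, and the quantity is session length, not staff-minutes. Similar totals would say little about how many people were needed or how long set-up took.
- *Preparation time.* Explored at interview; the article does not describe it as logged per session.
- *Reasons for non-completion.* Recorded, but described only for the frame programme and not linked to burden. The only reason carried into the outcomes table is orthostatic hypotension.

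**6. Scale.** Inputs: 50 participants in two arms, taken as 25 per arm (Sample size); a target of at least 5 sessions per week for 3 weeks (Intervention).

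- Planned sessions per frame participant: 5 × 3 = 15.
- Planned sessions in the frame arm: 25 × 15 = 375.
- Lost for staff or equipment reasons, assumed 10–20%: 0.10 × 375 = 37.5 and 0.20 × 375 = 75, so about 38 to 75 sessions.
- Contribution of those sessions to the burden indicator: 0.

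**7. Where the same losses would appear.** They reduce sessions completed. They also bear on the likely progression criterion that 80% of intervention participants adhere to at least five sessions per week. If exactly five sessions per week are planned and none is made up, one lost session puts a participant below the minimum. With all losses on as few people as possible, 38 sessions affect 3 participants (38 / 15 = 2.5, rounded up) and 75 affect 5 (75 / 15). Spread at one or more per person, either number could affect all 25. The loss is thus visible as adherence, but the planned summaries do not attribute it to staff.

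**The case against.** The strongest reply is that refusals are not the whole plan for burden. Physiotherapists are to be asked about it directly, in interviews and in a focus group, and the outcomes table names both as sources. In a feasibility trial with embedded qualitative work these are proper data. Sessions completed and reasons for non-completion are recorded, session minutes are compared between arms, and session content is recorded in both arms. The Case Report Forms and the content recording tool are not shown and may already hold staff numbers, coded reasons or set-up time.

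Most of this stands, and it limits the point. A reader might infer that zero refusals would be reported as no physiotherapist burden. The document does not say so: it sets no threshold and plans staff accounts beside the count. A reader might also infer that an undeliverable programme could pass unnoticed into a main trial. That is not supported either: burden is not among the likely progression criteria, and lost sessions would count against the adherence criterion, which is.

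The reply does not make patient refusal a measure of staff load. The interviews and focus group can explain burden but give no rate by arm or unit. The reasons for non-completion would supply one, but the article neither uses them for burden nor describes them for the control arm.

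**Conclusion.** The point holds as a fault in how one named feasibility outcome is defined. The article gives physiotherapist burden a single quantitative indicator, and that indicator measures patient behaviour. This goes beyond detail left to another document, because the article fixes the measure and fixes it badly. The practical risk is misattribution: sessions lost for staff or equipment reasons lower adherence, do not register as burden, and could be read as patient non-adherence.

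The size is modest. Of 375 planned frame sessions, every one lost for such reasons is invisible to the indicator. The figure of 38 to 75 rests on an assumed 10–20% loss, equal arms and the minimum target of five sessions per week; it illustrates scale and is not an estimate. No sample size, error rate or stated progression threshold changes. If the unseen forms already hold the needed fields, what remains is to name them as the indicator.

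**What to change.** 1. Keep refusals of sessions and assessments, and label them as the patient-burden indicator only.
2. For physiotherapist burden, report the share of planned sessions not delivered or shortened for staff or equipment reasons, by arm and unit. Obtain it by classifying the non-completion reasons already recorded as patient, staff or equipment, making sure that sessions never started are covered as well as those cut short. Record the same reasons in the control arm.
3. Log set-up minutes per session in both arms on the existing session form, if it does not already hold them.
4. Report these figures beside the interviews and focus group, which then explain them.
5. When adherence is reported against the progression criterion, show how many missed sessions were for staff or equipment reasons.

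The cost is a coded reason list and one numeric field, so a slightly longer form for treating physiotherapists. Treatment, sample size and assessment schedule are unchanged. Sessions already recorded can be classified only as far as the recorded reasons allow, and set-up minutes could be collected only from the date of the change.
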